### Intervention

Acupuncture will be performed with a disposable, sterilized, stainless steel needle measuring 0.20 × 30 mm (Dongbang Medical) in both groups. Ten acupoints (PC6, PC5, SP3, KI3, and ST36) will be chosen bilaterally for the intervention group (acupuncture group). The depth of acupuncture varies (1 to 1.5 cm) among the participants. After acupuncture needles are inserted, they will be manually manipulated to obtain a predetermined sensation, De Qi. Acupoints PC6 and PC5 will be inserted with depth adjustment to reach the anatomical plane right above the median nerve, thereby facilitating a more prominent sensation. Acupuncture will continue for 20 minutes. Ten other points that are not official acupoints and are not on the median or peroneal nerve will be chosen for the placebo group. An acupuncture needle depth of 0.5 cm will be used.

Acupuncture or placebo will be administered 2 times during the first and second visits. Administration will be done by a qualified acupuncturist who is a physician in Korean medicine with 10 years of clinical experience, independent of the anesthesia team.

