### Study Process

After a sufficient explanation of the purpose and methods of this clinical study by a researcher, subjects who voluntarily decide to participate and sign a written consent form will be evaluated for eligibility at the screening visit. Eligible subjects will be randomly assigned to the acupuncture or placebo control group according to randomization. Acupuncture treatment will be performed twice, one day before surgery (V1) and on the day of surgery (V2).

All intraoperative management and outcome assessments will be independently performed by anesthesiologists who are not involved in the acupuncture procedure. All participants will fast for 6-8 hours prior to surgery. After entering the operating room (V3), electrocardiography, pulse oximetry, and monitoring of the partial pressure of end-tidal carbon dioxide (IntelliVue MX550; Phillips North America Corporation) will be performed continuously. Automated oscillometric measurements of blood pressure at 2.5-minute intervals and “train of four” (TOF) (ToFscan; Drager Technologies) assessments will also be performed. Throughout the surgery, these data will be downloaded to personal computers using RS232C cables.

After checking the initial vital signs (heart rate, blood pressure, and oxygen saturation) (P1), anesthesia will be induced intravenously with propofol (1-2.5 mg/kg) and remifentanyl (0.01-0.1 ng/kg/min). Mask ventilation (P2) with desflurane will be performed after the administration of rocuronium (0.6-1 mg/kg). Once the TOF ratio reaches <2, the anesthesiologist will perform tracheal intubation (P3). The lungs of the subjects will then be ventilated with desflurane and oxygen in air (FiO2=0.5), and the tidal volume and ventilation rate will be adjusted to maintain the partial pressure of end-tidal carbon dioxide between 35 and 45 mmHg. An additional venous tube will then be secured (P4).

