### Outcome Measures

To investigate the efficacy of acupuncture on initial blood pressure fluctuations during laparoscopic hysterectomy, we will compare the difference between the highest and lowest mean blood pressures from the induction of anesthesia to the postincision period as the primary endpoint. As secondary outcomes, systolic, diastolic, and mean blood pressures will be compared at each predetermined timepoint. The incidence of hypotension (systolic blood pressure <90 mmHg or 80% of the baseline), hypertension (systolic blood pressure >160 mmHg or 120% of the baseline), tachycardia, and bradycardia will be recorded. The total use of remifentanil, surgical discontinuation, and length of hospital stay will be assessed as surrogate indicators of stable general anesthesia and surgical procedures.

For patient-reported outcomes, the Spielberger State-Trait Anxiety Inventory (STAI) and EQ-5D-5L will be used to evaluate changes in anxiety and the overall quality of life. The STAI was first validated in 1996 [16,17]. The STAI consists of 40 questions divided into 2 categories: 20 items assessing state anxiety and 20 items assessing trait anxiety. State anxiety refers to experiencing anxiety at the moment, while trait anxiety refers to the type and characteristics of anxiety.

The EQ-5D-5L will be used to assess the effects on the patient’s quality of life. The questionnaire consists of questions in 5 areas: mobility, self-care, usual activities, pain, and anxiety/depression. The EQ-5D-5L assesses the patient’s current state of health. Responses will be provided on a 5-point Likert scale [18].

The study process and timepoints are presented in Figure 1.

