### Statistical Analysis

Both intention-to-treat and per-protocol analyses will be performed, with intention-to-treat being the primary analysis. For per-protocol analysis, the study participants who successfully complete the surgery will be analyzed separately. Successful completion of the surgery is defined as the completion of the scheduled total laparoscopic hysterectomy under general anesthesia without protocol violations, conversion to open surgery, early termination due to intraoperative complications, or major deviations from the anesthetic protocol, such as changes in the anesthetic agents beyond the predefined regimen. For handling missing data, multiple imputations will be performed to obtain estimates and standard errors by setting 10 imputation sets.

The primary endpoint of this clinical trial is the difference between the highest and lowest mean blood pressure measured from anesthesia induction to the postincision period. The Student *t* test will be used to test whether the difference between the 2 groups in the primary endpoint is statistically significant. To account for potential confounding factors affecting the primary outcome, a multivariable linear regression analysis will be conducted. Covariates will include the placebo credibility score (at V1 and V2), anxiety levels (as measured by the STAI and EQ-5D), baseline ward blood pressure (V2), and preoperative blood pressure measured in the holding area prior to operating room entry (V3).

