In addition to the primary outcome, secondary outcomes will include hemodynamic stabilization time, incidence of hypotension and hypertension, comparison of drug use, and other efficacy endpoints, including STAI scores. Differences between the 2 groups will be compared using the Student *t* test or Wilcoxon rank sum test, unless otherwise specified. The 2 groups will also be compared by estimating the ratio between the blood pressure measured at each timepoint and that measured at V2, using the blood pressure at V2 as the baseline. Because blood pressure is measured repeatedly, it is not possible to assume independence between measurements; thus, generalized estimating equations will be used. To estimate this ratio, measurements will be log-transformed and included in the model. The 2 groups will be compared using the same method for the pulse rate measured at V2 and the pulse rate at each timepoint. To quantify the length of hospitalization in both groups, we will use Kaplan-Meier estimation to estimate the time until 50% of the participants are discharged. The log-rank test will be used to determine differences in the distribution of discharge times between the 2 groups.

The significance level for all analyses is set at .05. All statistical analyses will be performed using SAS 9.4 (SAS Institute, Inc) or R software 4.1 (R Foundation for Statistical Computing).

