Another strength of our design is the inclusion of psychological covariates to explore individual variability in response. Although not a primary or secondary endpoint, researchers have incorporated validated tools, such as the Spielberger STAI and EQ-5D-5L, to assess baseline anxiety and quality of life. These tools enable exploratory analysis of whether the psychological state moderates the physiological effects of acupuncture, helping to distinguish autonomically mediated responses from those influenced by psychological factors. This addresses a common limitation of prior acupuncture trials, which often did not account for patient-level psychological differences.

For our primary outcome, researchers chose absolute thresholds of MAP, rather than relative changes, due to inconsistencies in baseline blood pressure definitions in perioperative settings. Establishing a reliable baseline for relative changes is challenging, as preinduction blood pressure often differs from values obtained during preoperative evaluation [38], and normal blood pressure levels can vary depending on individual conditions and circadian rhythms [39]. Given these limitations, researchers have adopted standardized MAP thresholds: values below 65 mmHg are associated with impaired organ perfusion, while sustained elevations above 80 mmHg may increase the risk of major adverse cardiovascular events [40]. These thresholds align with intraoperative blood pressure management goals, providing a clear rationale for selecting them as our primary outcome measure. This standardization, along with the use of 2.5-minute noninvasive blood pressure monitoring, enables close tracking of blood pressure changes during the highly dynamic early intraoperative phase [41].

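### The repeated-measures ratios divide by the V2 blood pressure and pulse, which are recorded after acupuncture has begun

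*Protocol article*

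**What the plan says.** Four places in the protocol article bear on this.

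- **Timing of treatment.** Methods, Study Process: "Acupuncture treatment will be performed twice, one day before surgery (V1) and on the day of surgery (V2"). Methods, Intervention agrees: "Acupuncture or placebo will be administered 2 times during the first and second visits".
- **Reference value.** Methods, Statistical Analysis compares the groups by the ratio of each timepoint to V2, "using the blood pressure at V2 as the baseline", in a generalized estimating equations (GEE) model: "To estimate this ratio, measurements will be log-transformed and included in the model". Pulse follows: "The 2 groups will be compared using the same method for the pulse rate measured at V2". The same section lists "baseline ward blood pressure (V2") among the covariates of the adjusted primary model.
- **Event definitions.** Methods, Outcome Measures: "The incidence of hypotension (systolic blood pressure <90 mmHg or 80% of the baseline". Hypertension is defined in the same way, with 160 mmHg or 120%. No visit is named for this baseline.
- **Comment on baselines.** The Discussion, explaining the choice of primary outcome, says: "Establishing a reliable baseline for relative changes is challenging, as preinduction blood pressure often differs from values obtained during preoperative evaluation".

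The other pre-induction readings described are the holding-area pressure (V3) and the first operating-room vital signs (P1). Both come after the ward sessions. The readable text names no pressure or pulse taken before the first session as a reference.

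**The concern.** A baseline used to compare randomised arms should be untouched by treatment. Every V2 value follows at least the V1 session. Whether it also follows the second session is not stated. An arm difference already present at V2 is then built into the ratio at every later timepoint.

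This matters here because the Discussion says the two-session schedule was chosen so that acupuncture could take effect before the anaesthetics do. The ratio analysis is clean only if nothing has happened to pressure or pulse by V2. If something has, the ratios can show a difference where intraoperative pressures are equal, or show none where they differ.

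**Working it through.** The plan gives no figure for the ratio analysis, so there is none to reproduce. Its sample size concerns the primary endpoint and does not depend on V2.

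**1. What the ratio measures.** Let P be pressure at an intraoperative timepoint and V the pressure at V2. On the log scale, the between-arm contrast is

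[difference in mean log P] − [difference in mean log V].

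This holds whether each value is divided by V2 before modelling or V2 is the reference time in the GEE. Any arm difference at V2 is subtracted from the treatment comparison.

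**2. Equal intraoperative pressures.** If acupuncture moves resting pressure from B to B − e and P is the same in both arms, the ratio of ratios is B/(B − e) instead of 1. B and e are assumptions, because the article gives neither for this setting.

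| Assumed B (mmHg) | Assumed fall e (mmHg) | B/(B − e) | Spurious change |
|---|---|---|---|
| 130 (systolic) | 3 | 130/127 = 1.024 | +2.4% |
| 130 (systolic) | 5 | 130/125 = 1.040 | +4.0% |
| 130 (systolic) | 8 | 130/122 = 1.066 | +6.6% |
| 80 (mean) | 4 | 80/76 = 1.053 | +5.3% |
| 90 (mean) | 4 | 90/86 = 1.047 | +4.7% |
| 100 (mean) | 4 | 100/96 = 1.042 | +4.2% |

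Example: an intraoperative systolic pressure of 104 mmHg reads as 104/130 = 0.800 in one arm and 104/125 = 0.832 in the other. If acupuncture raised resting pressure by 3 to 8 mmHg, the sign would reverse: 130/133 = 0.977 to 130/138 = 0.942.

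**3. Effect on the test.** Assume a mean pressure of 90 mmHg, a log-ratio SD of 0.10 to 0.15, 24 patients per arm and a simple two-sample t comparison. A 4 mmHg fall at V2 shifts the log ratio by log(90/86) = 0.0455. With no intraoperative difference, the rejection rate is then 34% (SD 0.10) to 18% (SD 0.15) instead of 5%. The SDs are not in the article, so these rates show order of magnitude only.

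**4. Masking.** If acupuncture multiplies both V and P by the same factor k, the ratio is kP/kV = P/V and the contrast is 1. A real reduction during surgery would not be seen.

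**5. Event limits, only if their baseline is V2.** With B = 130 and a fall of 3 to 8 mmHg, the 80% limit moves from 104 to 101.6–97.6 mmHg (0.8 × 127 and 0.8 × 122). The 120% limit moves from 156 to 152.4–146.4 mmHg (1.2 × 127 and 1.2 × 122). The absolute limits of 90 and 160 mmHg do not move.

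**The case against.** The strongest reply is that the bias needs an effect the article does not claim. Its only figure, 4–10 mmHg, is for long-term use in uncontrolled hypertension. The Discussion adds that studies of 15–25 days showed no benefit, and it regards short-term effects as unsettled. Patients here are ASA class I or II, with interfering hypertension or hypotension excluded, and the rationale is bidirectional, so no net fall need be expected. If V2 is read before the second session, only carry-over from the previous day counts, and the Discussion puts the analgesic effect at a few hours. All of this stands: it makes the bias conditional and its size unknown. It does not turn V2 into a pre-treatment value.

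A second reply is that change from same-day, pre-anaesthetic pressure is a coherent measure of stability. That also stands, but such a change is then not an effect of acupuncture against baseline.

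Three stronger readings are tempting and not supported:

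- *The hypotension and hypertension counts are biased.* Outcome Measures names no visit for the baseline. The counts are exposed only if it is V2, V3, P1 or another post-needling reading.
- *The primary result is compromised.* The unadjusted t test on highest minus lowest mean pressure uses no baseline, and the planned absolute comparisons at each timepoint state no denominator. The adjusted primary model does use V2 and V3 as covariates, but the sizes above do not describe that model.
- *The Discussion forbids relative measures.* Its remark justifies the primary outcome only. It is a caution about baselines and does not contradict a secondary ratio.

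**Conclusion.** The point holds for the secondary ratio analyses of blood pressure and pulse. The stated denominator follows at least one treatment session, so any pre-anaesthetic effect of acupuncture is mixed into the comparison. This is an explicit rule in the article, not a detail left to another document.

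The size is conditional: zero if V2 is unaffected, and 2.4% to 6.6% on every ratio for an assumed fall of 3 to 8 mmHg from an assumed 130 mmHg. No percentage is given for event counts, because it would depend almost entirely on assumed intraoperative distributions.

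This should be fixed, but it is not critical: it touches secondary results in a trial that calls itself a pilot and exploratory.

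**What to change.** 1. Do not divide by V2 or use it as the reference time. Model log blood pressure and log pulse at each timepoint by GEE, with the log of a value recorded before the V1 session (screening or admission) as a covariate.
2. Name that same value as the baseline for the 80% and 120% limits, and report the absolute limits (below 90, above 160 mmHg) separately.
3. Add a fallback, because the readable text does not confirm that such a value was recorded and 35 of 48 patients were already randomised by June 2025. Without it, compare log blood pressure and log pulse between arms with no V2 denominator, and rest the event comparison on the absolute limits.
4. Report V2 descriptively. Present any change from V2 as change from the pre-anaesthetic level only.

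The cost is analysis wording, settled before unblinded data are seen so that it cannot look data-driven. A pre-V1 value lies further from surgery and is somewhat noisier, so some precision is lost. The fallback gives up the baseline adjustment altogether.

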## Results

Recruitment for the study commenced in October 2023 and is ongoing, with enrollment expected to continue through December 2025. The flow diagram of the trial is shown in Figure 2. As of June 2025, a total of 35 participants have been successfully recruited and randomized. Although the intervention and data collection procedures have been proceeding without major difficulties, the overall pace of recruitment has been slower than anticipated. This is primarily due to fluctuations in surgical scheduling and staffing capacity caused by medical strikes in the Republic of Korea [20].

**Figure 2 figure2:**
[figure not shown]
Flow diagram of the trial.

All participants enrolled thus far are female, reflecting the eligibility condition of requiring total laparoscopic hysterectomy. The mean age of the enrolled participants is 48.3 years. The current dropout rate is 11.4%, and up to the time of this protocol description, all reported adverse events have been mild and unrelated to the intervention.

Final data collection is projected to be completed by December 2025, which will be followed by data cleaning and statistical analysis through March 2026. Publication of the main study results is expected in the latter half of 2026.

## Discussion

The primary role of anesthesiologists during surgery extends beyond maintaining unconsciousness to actively minimizing the physical stress induced by intraoperative stimuli. These stimuli include not only surgical manipulation but also the administration of anesthetics and analgesics, which, while essential, can disrupt homeostasis and result in intraoperative hypotension. Factors, such as surgical bleeding and patient positioning, may exacerbate this effect. Even in patients without comorbidities, sustained hypotension has been associated with poor postoperative outcomes [21,22], and hypertensive episodes during surgery, often a sign of inadequate analgesia, are similarly linked to increased risks of major adverse cardiovascular events [3]. Thus, maintaining blood pressure within a target range is an important goal of anesthetic management.

Laparoscopic hysterectomy is a procedure often associated with significant hemodynamic fluctuations, particularly in the early intraoperative period. Pneumoperitoneum and Trendelenburg positioning may stimulate sympathetic activation or trigger vasovagal reflexes, resulting in rapid changes in blood pressure [15,23,24]. Anesthesiologists must anticipate nociceptive stimuli, such as tracheal intubation and skin incision, and preemptively adjust opioid administration to ensure hemodynamic stability [25,26]. However, due to interindividual variability and the pharmacokinetics of agents like remifentanil, achieving consistent control is challenging [27,28]. Although remifentanil’s rapid onset and offset allow precise titration, excessive dosing has been linked to adverse effects such as delayed emergence, postoperative nausea and vomiting, and opioid-induced hyperalgesia [29]. Because of these dose-related risks and the challenge of achieving consistent hemodynamic control, minimizing remifentanil use without compromising analgesia is a meaningful anesthetic goal. Reflecting this, the amount of remifentanil administered during the early surgical phase has been included as a secondary outcome in our study, aligning with the broader goal of minimizing opioid use while preserving analgesic efficacy [30,31]

Acupuncture has been proposed as a supportive technique to anesthesia, with studies reporting its potential to reduce anesthetic requirements, alleviate perioperative anxiety, and improve postoperative recovery [32,33]. Given its low invasiveness and favorable safety profile (characterized by mostly minor local reactions and rare treatment-requiring events), acupuncture remains a feasible adjunct in the perioperative setting [34]. Although its role in intraoperative blood pressure regulation remains under investigation, emerging evidence points to its influence on autonomic nervous system modulation. Functional magnetic resonance imaging studies have demonstrated that acupuncture alters hypothalamic connectivity, a key brain region involved in cardiovascular control [13]. Additionally, acupuncture has been shown to attenuate hemorrhage-induced hypotension in animal models and lower systemic blood pressure in patients with hypertension [10,35,36].

Outside the perioperative setting, acupuncture has shown clinically meaningful effects in reducing blood pressure among patients with essential hypertension. For example, studies by Flachskampf et al [35] and Yin et al [36] reported significant reductions in systolic and diastolic blood pressure after 6 to 8 weeks of repeated acupuncture sessions [10], whereas studies with shorter durations (15-25 days) failed to demonstrate such benefits [37]. Overall, although the long-term use of acupuncture therapy has blood pressure–lowering effects of 4-10 mmHg in patients with uncontrolled hypertension, the effects of short-term acupuncture therapy on blood pressure fluctuations have not yet been clearly established.

One important limitation in previous studies assessing acupuncture as an anesthetic adjunct is the timing and duration of stimulation [38]. Acupuncture requires adequate time to induce physiological effects, with analgesic effects typically emerging 20 minutes after needle insertion and lasting for just several hours. Therefore, acupuncture initiation only shortly before or during anesthesia may have different physiological potential, particularly because volatile anesthetics can suppress neural pathways responsive to acupuncture.

In this context, the selection of acupoints in the treatment group was based on previous studies demonstrating their physiological relevance in autonomic modulation and cardiovascular regulation. Specifically, PC5, PC6, and KI3 have been widely associated with reductions in perioperative anxiety and stabilization of heart rate variability, while ST36 is well-documented for its influence on vagal activation and blood pressure regulation. SP3 has been included for its role in supporting systemic homeostasis. For the selection of placebo acupoints, the following 3-fold strategy has been considered to minimize specific physiological stimulation: (1) if possible, a sham needle is preferable; (2) points should avoid all recognized World Health Organization acupoints and should not be situated along any known meridian pathways; and (3) anatomical regions are restricted to outside the limbs, where the treatment acupoints are applied. Since the use of nonpenetrating sham needles is not possible due to product discontinuation, the other 2 strategies have been used for the placebo group.

Our study protocol was designed to optimize the timing of acupuncture application, administering stimulation at 2 timepoints, once on the day before surgery and again on the morning of the surgery, which would allow a sufficient lead time before anesthesia induction. This schedule was chosen based on both clinical feasibility and physiological rationale. As patients are routinely admitted the day before laparoscopic hysterectomy, it is practical to deliver acupuncture during the hospital stay without requiring additional outpatient visits. Moreover, this repeated, preoperative approach provides a longer stimulation window than the approach in most prior studies evaluating acupuncture as an anesthetic adjunct, which typically applied stimulation only shortly before or during anesthesia. While the duration remains shorter than long-term outpatient regimens used for chronic hypertension, it represents a balanced and realistic timeframe to allow acupuncture’s physiological effects to manifest before the influence of general anesthetics begins, potentially enhancing its effectiveness in modulating intraoperative hemodynamics.

Another strength of our design is the inclusion of psychological covariates to explore individual variability in response. Although not a primary or secondary endpoint, researchers have incorporated validated tools, such as the Spielberger STAI and EQ-5D-5L, to assess baseline anxiety and quality of life. These tools enable exploratory analysis of whether the psychological state moderates the physiological effects of acupuncture, helping to distinguish autonomically mediated responses from those influenced by psychological factors. This addresses a common limitation of prior acupuncture trials, which often did not account for patient-level psychological differences.

For our primary outcome, researchers chose absolute thresholds of MAP, rather than relative changes, due to inconsistencies in baseline blood pressure definitions in perioperative settings. Establishing a reliable baseline for relative changes is challenging, as preinduction blood pressure often differs from values obtained during preoperative evaluation [38], and normal blood pressure levels can vary depending on individual conditions and circadian rhythms [39]. Given these limitations, researchers have adopted standardized MAP thresholds: values below 65 mmHg are associated with impaired organ perfusion, while sustained elevations above 80 mmHg may increase the risk of major adverse cardiovascular events [40]. These thresholds align with intraoperative blood pressure management goals, providing a clear rationale for selecting them as our primary outcome measure. This standardization, along with the use of 2.5-minute noninvasive blood pressure monitoring, enables close tracking of blood pressure changes during the highly dynamic early intraoperative phase [41].

Despite its strengths, our study protocol has several limitations. First, as with most acupuncture trials, blinding of the practitioner is not feasible. In this study, however, acupuncture is administered preoperatively by a certified traditional medicine physician in the ward, while intraoperative management and outcome assessments are independently performed by anesthesiologists in the operating room. This structural separation minimizes the risk of performance and detection bias. Additionally, outcome assessors remain blinded to group allocation throughout the trial. Second, this is a single-center exploratory study, which may limit the generalizability of the findings. Nevertheless, the trial’s methodological strengths, including the timing and repetition of acupuncture, the incorporation of psychological covariates, and the focused monitoring of intraoperative blood pressure, enhance its internal validity and potential clinical relevance.

In summary, this randomized controlled trial is designed to evaluate whether preoperative acupuncture, applied at 2 timepoints, can help stabilize intraoperative blood pressure during laparoscopic hysterectomy. By addressing both physiological mechanisms and psychological factors, the study aims to clarify the short-term effects of acupuncture on hemodynamic stability in a controlled surgical setting. The results may provide useful evidence on the feasibility and potential benefits of incorporating acupuncture into perioperative care to reduce blood pressure fluctuations and minimize opioid requirements.

